#### Data analysis and management

2.8.5

All data will be entered electronically. There will be a subject identification code list and each participant will receive a participant study identification number. Confidential documents will be retained in the institution's computer in the laboratory. A password system will be utilized to control access. Back up of data will be kept in locked cabinets in the laboratory as well.

The data set will be described via tables and figures containing values expressed as mean, standard deviation, median, minimum, and maximum values. The mean effects of the protocol and the group differences for all outcomes will be calculated using linear mixed models to incorporate terms for the protocols, sequence, and periods; a term referring to the carryover effect will also be added in order to control these effects.^[32]^

The effects will be related to differences of values in relation to the protocols, the sequences and the periods and it will be measured considering the value from the first moment of protocol and the value in the second time. The effects are listed below:The Protocols: Protocol 1: referring to intervention. Protocol 2: regarding the control.Sequences/Groups: Sequence/group 1: Related the sequence at the beginning of the study with the decubitus position with the limbs raised and NMES and ending with decubitus position with the limbs raised without NMES (Group 1). Sequence/group 2: Related to the sequence at the beginning of the study with the decubitus position with the limbs raised without NMES and ending with the decubitus position with the limbs raised and NMES (Group 2).Periods: period 1: related to the time of the first procedure. Period 2: related to the moment of the second procedure.

Estimated values and 95% confidence intervals are used to evidence the possible effects related to the studied factors. The *P* value is used to identify whether or not there was an effect of the protocol, the sequence, and the period. The level of significance will be set at 5%. Statistical analysis will be performed through the R version 3 (2013-05-16) (The R Foundation for Statistical Computing, Vienna, Austria) and SAS version 9.2 (SAS Inc., Cary, NC).

The sample size of 31 patients was based on the study of Stefanou et al^[18]^ for the variable CD34 + CD133 +, CD45− with effective detection of 7.3/10^6^ cells, standard deviation of 10.2, 5% alpha, and power of 80%.

The investigators will provide verbal and written feedback to relatives of participating patients about the results of the study and clinical conditions.

Any modifications to the protocol and administrative changes of the protocol will be communicated to ClinicalTrials.gov and Research Ethics Committee and clinical research unit of the Hospital das Clínicas da Faculdade de Medicina de Ribeirão Preto.

All principal investigators will have access to the final trial dataset.

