### Study design

2.1

This study is a randomized controlled crossover clinical trial with group 1 (starts with intervention and ends with control protocol) and group 2 (control and intervention protocol).

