### Randomization and allocation

2.4

This study will follow the recommendations of the Consolidate Standards of Reporting Trials (CONSORT)^[22]^ and the study protocol followed the Stardard Protocol Items for Randomised Trials (SPIRIT).^[23]^ After the consent, [name] will evaluate and determine the eligibility of patients. Thus, [name] will not be involved with the assessment and interventions that randomly allocates the participants in 1 of the 2 groups through a simple randomization (random numbers generated by the computer). The allocation sequence will be hidden by [name] through sequential numbered opaque sealed envelopes. After this step, [name] will open the envelope and will start the protocol. Blood sample analyses will be blinded to [name], [name], and [name].

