### Procedures

2.5

The study will be divided into 2 phases, the phase one will be held in the first 72 hours of septic shock; the phase two will be 3 days after the first assessment. Patients will be submitted in a random order to the intervention protocol (decubitus position with the limbs raised and NMES) and control (decubitus position with the limbs raised without NMES). The patients may be allocated in Group 1 (intervention and control) or group 2 (control and intervention) with a wash-out period of 4 to 6 hours between them as visualized in Fig. 1.

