#### Endothelial progenitor cells (EPCs)

2.6.1

To evaluate the EPCs, blood samples will be taken from an existing central venous access. The first 3 mL is discarded, and the remainder will be collected in 5 mL tubes with acid citrate and dextrose 5 minutes before the baseline and at the end of each protocol. The samples will be processed within 3 hours after collection and will be kept at 4°C during the procedure. The analysis will be performed by flow cytometry (BD Biosciences, FACS Canto ^TM^ II, EUA) and centrifuged at 700g for 20 minutes with no brake. The upper phase (plasma) will be removed gently and aliquoted at 0.25 mL. The lower phase containing the blood cells will be resuspended using 10 mL of cold 1 × PBS containing 0.5% (w/v) of BSA and 1.5 mM EDTA and it will be centrifuged again at 700g for 20 minutes with braking. The upper stage will be removed and discarded, the cell sediment will be resuspended, and 2.5 mL will be transferred to a separate tube and kept on ice.

Concurrently, 500 μL of sample will also be transferred in an isotype control and in 3 sample tubes with the appropriate antibodies. It will then be added to 9 mL of ACK lysis buffer to lyse red blood cells and incubated at room temperature (18°C–25°C) for 3 minutes. It will be washed twice with 9 mL cold 1 × PBS and finally centrifuged to 250*g* to 4°C with no brake for 5 minutes. Cell sediment will be resuspended twice in 500 μL of 1× PBS, and the samples will be filtered through 40 μm cell strainer in BD 5 mL Falcon tubes. Tubes will be kept at 4° C (or ice) in the dark before the flow cytometry. Different subpopulations of endothelial progenitor cells will be quantified by cellular markers by flow cytometry: CD34+/CD133+/CD45−, CD34+/CD133+/CD45−/VEDFR_2_e CD34^+^/CD45−/VEGFR_2_+.^[24,25]^ Nurses will receive a training in how blood sample will be taken, even as laboratory staff will be trained to evaluate cell progenitor endothelial.

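### Protocol, sequence, period and carryover cannot all be fitted in the stated two-sequence, two-period layout, so the primary estimate depends on which term gives way, and the plan does not say which

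*Protocol article*

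**What the plan says.** The Study design section defines two orders: "group 1 (starts with intervention and ends with control protocol) and group 2 (control and intervention protocol". The Procedures section separates the two sessions "with a wash-out period of 4 to 6 hours between them". It also plans a second phase three days after the first assessment.

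Section 2.8.5 (Data analysis and management) specifies a linear mixed model for all outcomes, with "terms for the protocols, sequence, and periods; a term referring to the carryover effect will also be added in order to control these effects". The time factor has two levels: "Periods: period 1: related to the time of the first procedure. Period 2: related to the moment of the second procedure". The response is described loosely as a difference between values, and "it will be measured considering the value from the first moment of protocol and the value in the second time". EPC samples are drawn "5 minutes before the baseline and at the end of each protocol", so the most natural reading is one change score per patient and period. P values are promised for protocol, sequence and period, but not for carryover. The model has no phase term.

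The same section bases 31 patients on a difference of 7.3 per 10^6 cells, SD 10.2, 5% alpha and 80% power. It does not say whether 10.2 is the SD of one period's result or of the within-patient difference.

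**The concern.** A two-sequence, two-period crossover supplies four sequence-by-period means. An intercept plus protocol, sequence, period and carryover asks for five quantities, and a random patient effect adds no fixed-effect information. In the AB/BA design, a carryover difference and a sequence difference cannot be told apart once protocol and period are in the model.

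Two things are at stake. First, the term is included in order to control carryover, which it cannot do in this layout, so the report might claim an adjustment that was not made. Second, the candidate estimates differ in kind. One is a within-patient contrast over both periods and the other a between-group contrast in period 1. A choice between them that is not fixed in advance could be made after the results are seen.

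**Working it through.** **Inputs.** Two sequences and two periods (sections 2.1 and 2.8.5). N = 31, difference 7.3, SD 10.2, 5% alpha, 80% power (section 2.8.5). Assumed because not stated: a two-sided test, a 15/16 split (allocation is by "simple randomization (random numbers generated by the computer"), and the between-period correlation rho.

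**The plan's own figure.** 2 × (1.960 + 0.842)² × 10.2² / 7.3² = 30.65, rounded up to 31. This is the per-arm size of a parallel comparison. It equals the total for a 2×2 crossover if the per-period SD is 10.2 and rho is 0. The figure reproduces and is not the error here.

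**Rank of the stated model.** Code NMES +1 and control −1, group 1 +1 and group 2 −1, period −1 and +1. Carryover is 0 in period 1 and the preceding protocol's code in period 2.

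| Cell | Intercept | Sequence | Period | Protocol | Carryover |
|---|---|---|---|---|---|
| Group 1, period 1 | 1 | 1 | −1 | 1 | 0 |
| Group 1, period 2 | 1 | 1 | 1 | −1 | 1 |
| Group 2, period 1 | 1 | −1 | −1 | −1 | 0 |
| Group 2, period 2 | 1 | −1 | 1 | 1 | −1 |

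In every row, carryover = 0.5 × sequence − 0.5 × protocol. The rank is 4 with 5 columns. Sequence, protocol and carryover are each non-estimable; intercept and period are estimable.

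**What each resolution estimates** (weights on the four cells, in table order, for NMES minus control):
- Carryover dropped: +0.5, −0.5, −0.5, +0.5. This is the period-adjusted within-patient estimate. If the carryover from NMES exceeds that from control by L, it enters only the second and fourth cells and shifts the estimate by −L/2. For an assumed L = 3.65 the expected value is 7.3 − 1.825 = 5.475; a simulation of 300 trials averaged 5.57.
- Sequence dropped: +1, 0, −1, 0. This is group 1 minus group 2 in period 1 only. A mixed model fitted to simulated data without sequence and with carryover returned exactly that difference.

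**Precision.** Let s be the per-period SD and h = 1/15 + 1/16 = 0.1292.
- Variance, period 1 only: s²h. Variance, within-patient: s²h(1 − rho)/2. The ratio is 2/(1 − rho), i.e. 2 at rho = 0 and 4 at rho = 0.5.
- If 10.2 is the per-period SD: the period-1-only SE is 10.2 × √0.1292 = 3.67 and noncentral t power on 29 df is 49%. With the carryover term removed, the SE is 2.59 (power 78%) at rho = 0 and 1.83 (97%) at rho = 0.5.
- If 10.2 is the SD of the within-patient difference: s = 10.2/√(2(1 − rho)), which gives, for period 1 only:

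| rho (assumed) | s | SE | Power |
|---|---|---|---|
| 0 | 7.21 | 2.59 | 78% |
| 0.3 | 8.62 | 3.10 | 62% |
| 0.5 | 10.20 | 3.67 | 49% |
| 0.7 | 13.17 | 4.73 | 32% |

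Under this second reading the within-patient SE is (10.2/2) × √0.1292 = 1.83 at any rho, with power 97%.

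**Do the two phases cure it?** With the order repeated in phase two and carryover acting within a phase only, the rank stays one short: 4 of 5 columns with period alone, 5 of 6 with a phase term added, 6 of 7 with four separate occasions. Two other models are full rank: one that also lets carryover run from phase one into phase two, and one that takes pre- and post-session values as separate responses. The article specifies neither.

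**The case against.** The strongest reply is that the problem may be harmless in practice. The plan lists protocol, sequence and period first and adds carryover afterwards. It defines sequence carefully and promises a P value for it, but none for carryover. Fitted in that order, the redundant column would be carryover, and the result would be the ordinary within-patient estimate with no loss of power. This stands as a likely outcome. It follows from a fitting convention that the plan does not state, however, and it leaves carryover uncontrolled despite the stated purpose of the term.

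A second reply is that a journal article condenses the full plan, so the response and the handling of phase may be set out elsewhere in a form that is full rank. That is fair as to missing detail. The list of model terms, though, is an affirmative statement, and it fails in the layout that the article itself describes.

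Three stronger readings are tempting and not supported:
- A reader might infer that the primary estimate must be either undefined or confined to period 1. The outcome in which carryover drops out shows otherwise.
- A reader might infer that carryover is aliased under every possible model of these data. The two full-rank models above show otherwise.
- A reader might infer, because both R and SAS are named, that the two packages would give different answers. The documents do not assign the model to either package and give no basis for this, and it was not tested.

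**Conclusion.** The point holds for the stated layout of two sequences, two periods and one change score per period. There the four terms cannot be estimated together, the protocol effect has no unique estimate, and the carryover term does not do what it is there to do. The change score is the natural reading of section 2.8.5, not a certain one.

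The loss of power is a conditional worst case, not the expected result. It arises only if sequence is the term given up. It then ranges from none relative to the 78% baseline (SD of the difference, rho = 0) through 49% to 32%, depending on the meaning of 10.2 and on an assumed correlation. If carryover is the term given up, power is unaffected and the cost is a bias of about half of any carryover difference, together with an unfounded claim of control. Because this is the analysis of the primary outcome and the correction is cheap, it should be made before data are analysed.

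**What to change.** Delete the carryover term. Specify the primary model as protocol, sequence and period as fixed effects with a random patient effect, and include phase explicitly when both phases are pooled. State which value per period is the response. The primary estimate is then the within-patient difference, NMES minus control, adjusted for period.

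State absence of carryover as an assumption resting on the planned wash-out. Examine it descriptively with samples already scheduled: pre-session EPC in period 2 minus pre-session EPC in period 1, by sequence, with 95% confidence intervals. Let no preliminary test of carryover or sequence choose the analysis.

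The cost is about one sentence on the model plus a short description of the check, with no new samples and no extra patients. The downside is that the report can no longer say that the model controlled carryover.

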#### Intervention protocol – decubitus position with the limbs raised and NMES

2.8.3

The patient will be positioned on a headboard at 30° in the decubitus position with the limbs raised to 20°. The location of the electrical current will be cleared with trichotomy when necessary. Adhesive electrodes 90 x 50 mm will be positioned in the gastrocnemius. The stimulator device will be the Neurodyn II (Ibramed, Sao Paulo, Brazil) to provide symmetrical biphasic pulses of 50 Hz, 250 μsec pulse duration, 2 seconds on (1 second of time of rise and 1 second of time of decay), and 5 seconds of rest during 30 minutes at an intensity capable of generating visible contractions and articular motion (Fig. 2).

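### Each session appears to be analysed as change from its own pre-value, without baseline adjustment; this is valid without carryover but less precise than adjusting for a value already collected

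*Protocol article*

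**What the plan says.** Section 2.6.1 of the protocol article has blood for endothelial progenitor cells (EPCs) drawn "5 minutes before the baseline and at the end of each protocol", so each session has a pre-value and a post-value, and the second session has its own baseline.

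Section 2.8.5 states how these values enter the analysis. It first describes the effects as contrasts: "The effects will be related to differences of values in relation to the protocols, the sequences and the periods". On how an effect is obtained from the two samples of a session, the same section adds that "it will be measured considering the value from the first moment of protocol and the value in the second time". The model is described as "linear mixed models to incorporate terms for the protocols, sequence, and periods; a term referring to the carryover effect will also be added". No baseline covariate is listed.

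The two sessions are run "with a wash-out period of 4 to 6 hours between them" (section 2.5), and a session lasts 30 minutes (sections 2.8.3 and 2.8.4).

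The sample size is given in the same section: "The sample size of 31 patients was based on the study of" an earlier NMES study, "with effective detection of 7.3/10^6^ cells, standard deviation of 10.2, 5% alpha, and power of 80" per cent.

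**The concern.** Read together, these sentences describe a change score: post minus pre within each session, compared between sessions. The difference between two change scores carries the noise of four measurements, and it fixes the slope on the baseline at 1 whether or not the data support that. Adjustment estimates the slope instead.

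At stake is the precision of the primary EPC comparison in a trial of 31 patients. The sample size section states no allowance for patients lost. If the planning SD is the SD of one session's change, the change-score analysis only just reaches its stated power.

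A second issue is the period 2 pre-value. In group 1 it is taken 4 to 6 hours after NMES and so may carry residual effect. How much this matters, and whether adjustment helps, has to be worked out separately for each analysis.

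**Working it through.** **The plan's own figure.** Inputs from section 2.8.5: difference 7.3, SD 10.2, alpha 5% (two-sided assumed), power 80%. The two-sample normal formula gives

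2 × (1.960 + 0.842)² × 10.2² / 7.3² = 30.65, rounded up to 31.

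This is a per-arm figure for a parallel comparison. It equals 31 crossover patients if 10.2 is the SD of one session's analysed value and sessions are uncorrelated, so that the within-patient difference has SD 10.2 × √2 = 14.42. The document does not say which SD 10.2 is.

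**Precision.** For each patient let Dpre and Dpost be the between-session differences in pre-values and post-values. Assume equal variance V and correlation r.

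- Change score: Var(Dpost − Dpre) = 2V(1 − r).
- Adjusted: residual variance of Dpost given Dpre = V(1 − r²).
- Ratio, adjusted to change: (1 − r²) / [2(1 − r)] = (1 + r)/2.

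With within-session correlation rw and between-session correlation rb, r = (rw − rb)/(1 − rb). The document gives none of these, so a range is shown.

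Estimating the slope costs one degree of freedom. With 31 patients and a model of intercept, sequence and Dpre, the variance rises by a factor of about 1 + 1/27 = 1.037. The last column multiplies 30.65 by the ratio. It assumes that 10.2 is the SD of a session's change with uncorrelated sessions, and it leaves the penalty out.

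| r | (1+r)/2 | with penalty | patients for 80% power (change score: 31) |
|---|---|---|---|
| 0 | 0.50 | 0.52 | 16 |
| 0.3 | 0.65 | 0.67 | 20 |
| 0.5 | 0.75 | 0.78 | 23 |
| 0.7 | 0.85 | 0.88 | 27 |
| 0.8 | 0.90 | 0.93 | 28 |
| 0.9 | 0.95 | 0.99 | 30 |

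Simulated trials of 31 patients agree. The ratio was 0.51 at r=0. At r=0.6 (rw 0.8, rb 0.5) the standard errors were 1.49 adjusted and 1.65 for change, a ratio of (1.49/1.65)² = 0.82 against an expected 0.80 × 1.037 = 0.83. Without carryover both estimators were unbiased.

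Two thresholds follow. Below r = 0.5 the change score is less precise than ignoring the baseline, since 2(1 − r) > 1. Above r = 2/1.037 − 1, about 0.93, the lost degree of freedom outweighs the gain, by at most about 4%.

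**Residual NMES effect.** Let Lb and Lp be the residual effect at the period 2 pre-sample and post-sample in group 1, and beta the slope on the baseline.

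- Bias of the change score: (Lb − Lp)/2.
- Bias of the adjusted analysis: (beta × Lb − Lp)/2.

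Suppose 25% of a 7.3 effect remains at the pre-sample, so Lb = 1.83. If it vanishes entirely by the post-sample, the change-score bias is 1.83/2 = 0.91, or 12% of 7.3. If it persists unchanged, the bias is 0.

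Under exponential decay, a fraction f surviving 4 hours falls by a further factor f^(0.5/4) over 30 minutes. With beta = 0.6 (assumed):

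| f | Lb | Lp | change-score bias | adjusted bias |
|---|---|---|---|---|
| 10% | 0.73 | 0.55 | +0.09 | −0.05 |
| 25% | 1.83 | 1.53 | +0.15 | −0.22 |
| 50% | 3.65 | 3.35 | +0.15 | −0.58 |

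The change-score bias is about 2% of 7.3 at most in these cases. The gap between samples may exceed 30 minutes, because the pre-sample comes 5 minutes before baseline and section 2.7.1 also has calorimetry at baseline, with 30-minute recordings. With 5 + 30 + 30 = 65 minutes the exponent is 65/240, and the f = 50% case gives Lp = 3.03 and a change-score bias of (3.65 − 3.03)/2 = 0.31, about 4%. The adjusted bias is then (2.19 − 3.03)/2 = −0.42.

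**The case against.** **The wording is loose.** Section 2.8.5 names two values without writing out a subtraction, and it does not expressly exclude a baseline covariate. A condensed article may leave covariates to a fuller document. This stands as a caution: the change score is the natural reading, not a certainty. But the section does say how the effect is measured and does list model terms, so the sentence needs clarifying in either case.

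**The choice is about efficiency, not validity.** Without carryover the change score is unbiased. The gain depends wholly on an r that is not given. Samples within a session are much closer in time than samples 4 to 6 hours apart, so r could be high and the gain small. This stands, and it limits the size of the point.

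**A reader might infer that the change score materially inflates the NMES effect and that a baseline covariate cures this.** The documents do not support either step. The 12% figure needs a residual that survives the wash-out and then disappears within one session. Ordinary decay gives a few per cent, a persisting residual cancels, and a residual still rising would reverse the sign. No EPC time course is given. The covariate carries the same residual: in the three decay cases tabulated, adjustment has the larger bias in two.

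**A reader might also infer that 31 patients is wrong or that carryover is ignored.** Neither follows. The stated 31 reproduces. At that size the change score has 80% power by the normal formula (78% by t-test) if 10.2 is the SD of a session's change with uncorrelated sessions, and 97% if it is the SD of the within-patient difference. The plan does include a carryover term. That term cannot be separated from sequence in the session outcomes of one two-period phase, but this is a different point.

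**Conclusion.** The point holds on precision and clarity. As most naturally read, the plan forgoes adjustment for a baseline it already collects. The variance cost ranges from a doubling (r = 0) to nothing worthwhile (r above about 0.9), and r is unknown. The arithmetic assumes equal variances of the pre and post differences and complete data in both sessions. The gain matters most if 10.2 is the SD of a session's change. On other readings of that SD, power is already high.

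On bias, only a conditional statement survives. Residual NMES effect at the period 2 pre-sample biases the change score if it fades during that session, and it biases the adjusted analysis by an amount that can be smaller, larger or of opposite sign. This is no reason to prefer one analysis over the other.

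**What to change.** State the analysis variable explicitly. Make the primary model the end-of-session value with the session pre-value and the patient's mean pre-value as covariates, protocol, period and sequence as fixed effects, and patient as a random effect. Including the patient mean keeps the adjustment within patient, so with both sessions complete the model is equivalent to regressing the between-session post difference on the between-session pre difference.

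Report the change-score result as supportive and compare the two. A marked disagreement would be a prompt to look at the period 2 pre-values for residual effect. Neither result should be presented as correcting for an inadequate wash-out; the 4 to 6 hour interval needs its own justification.

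The cost is a change of wording and one degree of freedom, about 4% in variance at 31 patients. No new samples, visits or patients are needed.

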Combining the pathophysiology of septic shock, the role of EPCs, the effects of NMES, and the divergence of results of the studies using NMES in patients in septic shock, we hypothesized that NMES initiated an early phase of septic shock and could contribute favorably to the mobilization of EPCs without causing metabolic and hemodynamic impairments. Therefore, the objective of this study is to investigate the effects of NMES in patients with septic shock.

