## Discussion

3

Septic shock is a potentially fatal organ dysfunction caused by an imbalance of the host response to infection. This disease is life-threatening circulatory failure with inadequate tissue perfusion because changes may occur in microcirculation and occurs alterations in endothelial barrier function.^[5]^

Indeed, the endothelium is responsible for the interface between tissues and the blood compartment and participates in the local regulation of blood flow and vascular caliber.^[6]^ Studies have been shown the relation between EPCs and their neovascularization capability in adult ischemia tissue and participation in the formation of new blood vessels.^[7,33]^

Physiotherapy can use NMES in critically ill patients. It has been demonstrated that NMES is well tolerated and it seems to have a short-term systemic effect on the peripheral microcirculation, potential benefit acute activation of microcirculation observed by the increased rate of oxygen consumption and reperfusion as measured by infrared spectroscopy.^[20,21]^

Therefore, this work will demonstrate the possible beneficial effects of electrical stimulation as evaluated by the mobilization of endothelial progenitor cells in patients with septic shock. It will determine whether electrical stimulation can be applied in critically ill patients without causing harmful metabolic and/or hemodynamic changes.

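### The plan tests every outcome with a 5% P value and ties no other criterion to its no-impairment claim, so a non-significant metabolic or hemodynamic result could be read as no harm

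*Protocol article*

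**What the plan says.** **The aim.** The Introduction of the protocol article ends with a two-part hypothesis: NMES mobilises endothelial progenitor cells (EPCs), and does so "without causing metabolic and hemodynamic impairments". The Discussion turns the second part into a promised result: "It will determine whether electrical stimulation can be applied in critically ill patients without causing harmful metabolic and/or hemodynamic changes".

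**The analysis.** Section 2.8.5 covers every outcome with one model: "The mean effects of the protocol and the group differences for all outcomes will be calculated using linear mixed models". Estimates are planned: "Estimated values and 95% confidence intervals are used to evidence the possible effects related to the studied factors". The next sentence gives the inferential rule: the P "value is used to identify whether or not there was an effect of the protocol, the sequence, and the period". The significance level is 5%.

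**The outcomes concerned.** They are oxygen consumption, carbon dioxide production and resting energy expenditure (section 2.7.1), and heart rate, blood pressure, oxygen saturation and breathing frequency (section 2.8.1). No SD, expected change or limit of acceptable mean change is given for any of them.

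**Adverse events.** Section 2.8.4 lists per-patient thresholds. Crossing one interrupts the session and the event is reported.

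**Sample size.** Section 2.8.5 sets 31 patients on one EPC subpopulation, "with effective detection of 7.3/10^6^ cells, standard deviation of 10.2, 5% alpha, and power of 80"%.

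**The concern.** A test of no difference can support a claim that an effect exists. It cannot, by failing, support a claim that none exists. Section 2.8.5 nevertheless uses the P value in both directions (whether or not), and does so for the outcomes on which the no-impairment claim rests. Followed as written, a blood pressure or oxygen consumption result with P>0.05 would be recorded as no effect of the protocol. The Discussion would then have its conclusion that NMES can be applied without harmful change.

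Under such a rule, imprecision favours the desired answer: the fewer evaluable patients and the noisier the measurement, the more easily the trial finds no harm. The population is patients in the first 72 hours of septic shock, so a reassurance that reflects only low precision could be carried into practice.

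**Working it through.** **1. The plan's own figure.** Inputs from section 2.8.5: difference 7.3, SD 10.2, two-sided alpha 5% (sidedness is not stated; two-sided reproduces the figure), power 80%.

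n = 2 × [10.2 × (1.960 + 0.842) / 7.3]² = 30.65, rounded up to 31.

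The stated 31 reproduces, using the formula for two independent means. No metabolic or hemodynamic variable enters it. That is ordinary sizing on the primary outcome, but it means the precision for the other outcomes has to be worked out separately.

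**2. Units.** The documents give no SD for these outcomes. I therefore express a true harmful mean shift as d, in SDs of the within-patient NMES-minus-control difference, and assume 31 complete patients. The crossover contrast has 31 − 2 = 29 degrees of freedom.

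**3. Precision.** CI half-width = t(0.975, 29)/√31 = 2.045/5.568 = 0.367 SD. The shift detectable with 80% power is (1.960 + 0.842)/√31 = 0.50 SD.

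**4. Chance that a real harmful shift gives P>0.05.** This is one minus the power of the two-sided 5% t test, from the non-central t distribution with non-centrality d√31:

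| True shift d (SD of difference) | Non-centrality | P>0.05 in |
|---|---|---|
| 0.2 | 1.11 | 81% |
| 0.3 | 1.67 | 63% |
| 0.4 | 2.23 | 42% |
| 0.5 | 2.78 | 23% |
| 0.6 | 3.34 | 10% |
| 0.7 | 3.90 | 4% |

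With 25 evaluable patients the 0.5 SD figure rises to 33%, and with 20 to 44%.

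**5. The same in raw SD units.** With within-patient correlation ρ, the SD of the difference is √(2(1 − ρ)) raw SDs. A harm of 0.5 raw SD gives P>0.05 in 52% of trials at ρ = 0, 23% at ρ = 0.5 and 6.5% at ρ = 0.7. For 0.3 raw SD the figures are 79%, 63% and 45%.

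**6. Adverse events.** If 0 of 31 patients have an event, the exact two-sided 95% upper limit is 1 − 0.025^(1/31) = 11.2% (one-sided 95%: 1 − 0.05^(1/31) = 9.2%). This counts patients, not sessions.

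**7. What a CI criterion would give.** Suppose NMES truly makes no difference, and no impairment is claimed only if the 95% CI excludes a limit m on the harmful side. The claim then succeeds in about 37% of trials for m = 0.3 SD, 58% for 0.4, 77% for 0.5 and 90% for 0.6. Requiring the CI to lie inside ±m on both sides is stricter: about 1%, 18%, 54% and 80% by simulation for the same four values.

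**The case against.** Several points on the other side are sound.

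- **The CIs are already planned.** Section 2.8.5 announces estimates and 95% intervals just before the P-value sentence, and a careful reader could see from them what was not excluded. This stands, and it makes the repair cheap. But the intervals are compared with no limit, and the whether-or-not judgement is given to the P value.
- **Harm is also defined per patient.** The section 2.8.4 thresholds are absolute and do not depend on a mean-difference test. This stands too. They do not cover oxygen consumption, carbon dioxide production or energy expenditure, however, and they are not linked to the no-impairment conclusion.
- **EPCs are the primary outcome.** Basing 31 patients on them is normal and is not counted here as a fault.
- **A margin may be in the full analysis plan.** Its absence from an article would be no finding. The finding is the rule that the article does state.
- **The size is not anchored.** Nothing in the documents shows that 0.3 or 0.4 SD is harmful, and from 0.6 SD upwards misses are uncommon. For oxygen consumption even the harmful direction is debatable, because the Discussion treats a raised rate as a potential benefit.

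A reader might infer that the investigators have declared non-significance to be their proof of safety, or that the P value is the only evidence on harm. The documents support neither. The P-value sentence is a general one about model terms, no passage connects it to the Discussion's claim, and intervals and adverse events will be reported beside it.

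**Conclusion.** The point holds in a limited form. The article promises a conclusion about absence of harm, states a whether-or-not P-value rule for all outcomes, and ties neither its CIs nor its adverse-event limits to that conclusion. A non-significant result could therefore be read as no harm.

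How often this would mislead depends on the true shift: in most trials at 0.3 SD of the within-patient difference or less, in about one in four at 0.5 SD, and seldom above 0.6 SD. These figures assume 31 complete patients and an SD unit that the documents do not supply. Fewer evaluable patients worsen them; in raw units, high within-patient correlation improves them. The matter affects secondary and other outcomes, not the EPC analysis. It should be corrected but does not threaten the main result.

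**What to change.** 1. In section 2.8.5, add that for metabolic and hemodynamic outcomes P>0.05 will not be read as absence of impairment, and that the conclusion rests on the NMES-minus-control estimate with its planned 95% CI.
2. Report adverse events separately for the NMES and control protocols, with exact 95% limits.
3. Reword the Discussion sentence, and the matching part of the hypothesis in the Introduction, as estimation of the metabolic and hemodynamic effects. Alternatively, keep a no-impairment claim only for outcomes where the CI excludes a harm-direction limit that the investigators choose and record before the data are analysed. Otherwise report that impairment was not excluded. Timing by unblinding would not suit, because section 2.4 describes blinding only for the blood sample analyses.

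A limit on the harmful side is enough; two-sided equivalence for every outcome would be much harder to meet.

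**Cost.** This takes a few sentences and, under the second option, a limit and a harmful direction for each chosen outcome. It needs no extra patients or measurements. The price is a less favourable safety conclusion when the CI is wide: even with no true difference, a one-sided limit of 0.5 SD is met in about 77% of trials and one of 0.3 SD in about 37%. The estimation wording avoids that and is the simpler choice.
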